### Analysis

The primary and secondary outcomes will be analysed using a Poisson regression model to estimate the relative risk of developing each outcome with preincision compared with postcord clamping antibiotics. We will assess for overdispersion and if high, consider other models, such as a negative binomial. Appropriate considerations will be made to allow for the autocorrelation of data. We will look at the autocorrelation and partial autocorrelation plots to ensure any autocorrelation is accounted for. An adjustment for calendar time will be included in the model to allow for season effects. We will include terms for year, age and the interaction between them and mode of delivery (CS or vaginal). The key outcome parameter will be estimated by an additional term to identify those who receive preincision rather than postcord clamping antibiotics.

Rather than being described in dichotomous form, we will estimate the probability of preincision antibiotics using data from the national survey and known hospital policy. The estimated coefficient will provide an estimate of the change in policy, adjusting for misclassification.

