### Objectives

The primary objective of the study is to investigate whether preincisional in-utero exposure to antibiotics immediately prior to birth (Intervention) compared with no preincisional antibiotic exposure (Comparator) increases the risk of 1) asthma and 2) eczema (Outcomes) in children born by CS (Population). The relationship between antibiotic exposure and asthma and eczema severity (defined based on prescribing information and hospital admission data) will also be explored.

Secondary objectives:

Investigating the effect of preincision prophylactic antibiotics in children born by CS on: a) other allergic and allergy-related diseases; b) autoimmune diseases; c) infections and inflammation; d) other immune system-related conditions; e) neurodevelopmental conditions; f) less specific measures of child health (colic and failure to thrive).Investigating the effect of preincision prophylactic antibiotics in children born by CS on health service utilisation (overall consultation frequency in primary care and hospital admissions).Investigating if the effects of a reduction in postpartum maternal infectious morbidity shown in randomised controlled trials outside the UK can be replicated in the UK using routine healthcare data.

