Urinary tract infection/cystitis/pyelonephritis		x	x
Sepsis		x	x
Pelvic abscess		x	x
Maternal death (if infection related)*†			x
Antibiotic prescribing*		x	
Length of hospital stay*			x

*Exploratory outcome due to insufficient evidence base, including lack of longitudinal studies investigating the association between microbiota/early antibiotic exposure and outcome of interest;

†Tabulation if the outcome is very rare.

ADHD, attention deficit hyperactivity disorder; ITP, thrombocytopenic purpura; SLE, systemic lupus erythematosus.

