### Estimates of sample size and statistical power

To obtain estimates of statistical power and to estimate the impact of misclassification on estimates of increase in risk with prophylactic antibiotics before CS, we simulated the study (1) based on our estimates using the THIN database regarding the number of children with linked maternal data and asthma diagnosis rates in each year group between birth and 5 years of age, in line with previously published figures,^31^ and (2) using HES data based on estimates of children with linked maternal data and rates of children newly hospitalised for asthma assuming a readmission rate during the follow-up period of 50% based on HES statistics.^25^

In each simulation, we created a dataset for the whole study, with 13 birth cohorts from 2006 to 2018, and follow-up included across the first 5 years of life (curtailed at the end of 2018) (table 2). Each birth was classified by mode of delivery, and for those delivered by CS, whether antibiotics were given before skin incision, generated randomly using a binomial random number generator using an underlying probability of exposure to preincision antibiotics during that year of birth.

**Table 2 T2:** The number of births, years of follow-up and expected events in each simulation

	THIN-CPRD database	HES database
CS births	206 615	2 070 500
Postclamping antibiotics	111 508	1 115 670
Preincision antibiotics	95 107	954 830
VD births	570 774	5 973 100
Total births	777 389	8 043 600
CS person years of follow-up	792 265	8 661 832
Postclamping antibiotics	501 401	5 524 890
Preincision antibiotics	290 864	3 136 942
VD person years of follow-up	2 215 405	25 339 526
Total person years of follow-up	3 007 670	34 001 358
New events in children born by CS	7173	15 333
Postclamping antibiotics	5324	10 454
Preincision antibiotics	1849	4880
New events in children born by VD	20 378	44 906
Total events	27 551	60 240
Average event rate per 1000 person years	9.2	1.8

CPRD, Clinical Practice Research Datalink; CS, caesarean section; HES, Hospital Episode Statistics; THIN, The Health Improvement Network; VD, vaginal delivery.

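### For outcomes analysed as repeated counts, the remedies named in the Analysis section do not reliably allow for correlation between one child's age-years; child-clustered variance should be the default

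*Protocol article*

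**What the plan says.** The Analysis section of the protocol article gives one model for everything: "The primary and secondary outcomes will be analysed using a Poisson regression model to estimate the relative risk of developing each outcome". Its terms are stated as "We will include terms for year, age and the interaction between them and mode of delivery (CS or vaginal"), plus a term for preincision antibiotics. On variance it says "We will assess for overdispersion and if high, consider other models, such as a negative binomial". It continues "Appropriate considerations will be made to allow for the autocorrelation of data" and "We will look at the autocorrelation and partial autocorrelation plots to ensure any autocorrelation is accounted for".

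Secondary objective 2 concerns "health service utilisation (overall consultation frequency in primary care and hospital admissions"). Table 1 lists consultations, admissions and child antibiotic prescribing with an asterisk, which its footnote explains as "Exploratory outcome due to insufficient evidence base".

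Under Methods, exposure is assigned by year of birth in primary care data and by the hospital's policy year in secondary care data, so it does not change as a child ages. The sample size section simulates "follow-up included across the first 5 years of life (curtailed at the end of 2018"). The only random effect named is for hospital, as a sensitivity analysis. The exclusion criteria address independence only between children of a multiple birth.

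**The concern.** An age term requires follow-up to be split by age. One child then contributes up to five rows, or the same children recur in successive age cells of their birth cohort. For a first diagnosis this does no harm, because a child has at most one event. Consultation frequency is different: a child seen often at age 1 tends to be seen often at ages 2 to 4. Exposure is the same on all of a child's rows, so this correlation passes directly into the variance of the preincision coefficient.

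The remedies that the article names do not target this. A negative binomial model enlarges the variance of each row but still adds a child's rows up as independent. Autocorrelation and partial autocorrelation plots are tools for serial dependence in a time series and do not identify the child as the cluster.

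At stake is a spurious finding of harm or benefit on health service use, a numbered objective. The size of the databases gives no protection: a proportional error in the standard error does not shrink as the sample grows.

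**Working it through.** **The plan's own figures.** The article states no precision or power for consultations, admissions or prescribing, so there is no figure to reproduce for these outcomes. The asthma rates in Table 2 do reproduce: 27 551 / 3 007 670 = 9.16 and 60 240 / 34 001 358 = 1.77 per 1000 person-years (stated 9.2 and 1.8).

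**Inputs.** From the article: 13 birth cohorts (2006-2018), up to five years of follow-up curtailed at the end of 2018, and the uptake values 0, 0.2, 0.4, 0.6, 0.8, 1 in the sample size section. Assumed, because the article gives none: mean count per child-year and between-child variance.

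**Step 1: design effect by formula.** Let mu be the mean per child-year, th the variance of a gamma child effect that persists over all ages, and m = 5 years.

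- Against Poisson rows: 1 + th·m·mu.
- Against negative binomial rows: (1 + th·m·mu) / (1 + th·mu).

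| Assumed outcome | mu | th | Poisson rows | SE factor | Neg. binomial rows | SE factor |
|---|---|---|---|---|---|---|
| Consultations | 6 | 0.5 | 1 + 15 = 16 | 4.0 | 16/4 = 4.0 | 2.0 |
| Antibiotic prescriptions | 0.6 | 1 | 1 + 3 = 4 | 2.0 | 4/1.6 = 2.5 | 1.58 |
| Admissions | 0.2 | 2 | 1 + 2 = 3 | 1.73 | 3/1.4 = 2.14 | 1.46 |
| Rare event at the asthma rate | 0.0092 | 1 | 1.05 | 1.02 | 1.04 | 1.02 |

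These are high-end factors, because all between-child variation is taken as permanent. The last row shows why a rare first event is essentially untouched.

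**Step 2: weaker and stronger correlation.** Null simulation with a child-level and a child-year-level gamma effect; terms for birth year, age, mode and age by mode. With R the ratio of child-clustered to row-level (negative binomial type) SE, the implied type I error is 2·(1 − Phi(1.96/R)).

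| Mean per year | Count correlation | R | Implied type I error |
|---|---|---|---|
| 4 | 0.07 | 1.11 | 7.7% |
| 4 | 0.21 | 1.31 | 13.5% |
| 4 | 0.35 | 1.48 | 18.5% |
| 4 | 0.49 | 1.63 | 22.9% |
| 0.5 | 0.04 | 1.07 | 6.7% |
| 0.5 | 0.13 | 1.20 | 10.2% |
| 0.5 | 0.21 | 1.31 | 13.5% |
| 0.5 | 0.30 | 1.42 | 16.8% |

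Direct rejection rates at mean 4 and correlations 0.21, 0.35, 0.49 (500 datasets each):

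- negative binomial on child-years: 13.6%, 17.2%, 21.4%;
- quasi-Poisson on birth-year by age by mode cells: 16.4%, 22.6%, 28.8%.

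**Step 3: with the year-by-mode term.** Step 2 omits the interaction of year with mode that the Analysis section includes. Two further null simulations added it, with a linear year trend.

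- 200 replicates of 6000 children, using the first three rows of the Step 1 table. Coverage of nominal 95% intervals was 73-88% for negative binomial rows, 68-87% for quasi-Poisson cells and 92-96% with child-clustered variance.
- A separate run under assumed means and frailties rejected in 14-24% for scale-corrected cells and 5-6% with child-clustered variance. A lag-1 autocorrelation check along birth cohorts detected the dependence in only 18-91% of runs, depending on the setting.

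The direction is therefore the same with and without that term.

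**The case against.** A reader might infer that the plan treats a child's age-years as independent and that its intervals are too narrow. The article says neither. It gives no unit of analysis (child, child-year or cell) and no variance estimator, and a child-clustered Poisson model would have the same terms. It commits openly to allowing for autocorrelation, which may be meant to include within-child correlation, and it offers the negative binomial only as an example. A journal article commonly leaves the choice of variance estimator to the full analysis plan. All of this stands, so the point cannot be put as an established error.

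A reader might also extend the point to all of health service use, prescribing and infections. Only consultations are described as a frequency. The phrase about developing each outcome fits first events, and the other outcomes are affected only if episodes are counted.

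The size is open too. It rests wholly on assumed inputs, and with weak correlation the excess is small. Much larger error rates under plain Poisson can be calculated, but they describe an analysis that the overdispersion check is meant to replace.

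What remains is narrower. Where the article does name remedies, those remedies do not reliably deal with this dependence, and whether anything is done is left to checks that can miss it.

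**Conclusion.** The point holds for outcomes analysed as repeated counts: clearly primary care consultation frequency, and conditionally admissions, child antibiotic prescribing and infections. If only the named remedies are applied, the type I error of the preincision term is about 7-8% with weak within-child correlation and about 14-29% with moderate to strong correlation, against about 5% with child-clustered variance. The 29% upper end comes from the model without the year-by-mode term; the separate run with that term gave 14-24%. Every percentage depends on assumed means and correlations that the article does not supply, so the direction is firm and the size is not.

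Consultations, admissions and child antibiotic prescribing are exploratory secondary outcomes. Asthma, eczema and other first-diagnosis outcomes need no change on this account.

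**What to change.** Add one sentence to the Analysis section. For outcomes analysed as repeated counts, keep the stated mean model and base confidence intervals on a variance clustered on the child, or on a higher level that contains the child, by default and not conditional on the overdispersion or autocorrelation check. The same sentence should say which outcomes are counted as repeated episodes and which as first events.

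GEE or a child random effect could also address the dependence, but they rest on different assumptions and are not interchangeable with a clustered variance. Collapsing to one total per child would not support the age and age-by-mode terms.

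The cost is wider intervals for these outcomes, data held at child level rather than as aggregated cells, and more computing time, chiefly in the full HES dataset. If the team already intends this, the sentence only records it.

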**Ethics and dissemination:**

Ethical approval has been obtained from the University of Birmingham Ethical Review Committee with scientific approvals obtained from the independent scientific advisory committees from the Medicines and Healthcare products Regulatory Agency for CPRD and the data provider, IQVIA for THIN. The results will be published in peer-reviewed journals, presented at national and international conferences and disseminated to stakeholders.

Strengths and limitations of this studyA large sample size including mother-child linked data from two nationally representative primary healthcare databases and a secondary healthcare database.Investigation of a broad range of relevant child outcomes including severity.Investigation of maternal outcomes using real world evidence to confirm findings reported in randomised controlled trials.Use of a comparison group of vaginally delivered children to effectively control for changes in diagnosis, recording and exposures over time.Timing of prophylactic antibiotic administration is not recorded in routine healthcare data; therefore, analysis is based on the estimated proportion of hospitals with the preincision antibiotic policy in each year during the study period.

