We have a proposed linkage strategy which has already been validated by another recent study using matching algorithms based on HES data using organisation codes, admission dates, birth dates, general practice codes, sex, gestation and maternal age plus a number of other variables common to birth and maternity records. The database remains nationally representative for the main birth characteristics (such as gestational age, birth weight, sex and maternal age).^27^ The final output of this process will be a linked HES data set in which details of birth events and subsequent admissions of the children associated with these events can be elucidated.

HES alone, however, cannot be used to identify timing of prophylactic antibiotic administration and prophylactic antibiotics given. We will obtain the time point after which preincision antibiotic policy was introduced in each hospital from a national survey of maternity care providers in the UK. All maternity units undertaking CSs were included in the survey with a target response rate of 85%.

The exposure and outcome measures in the healthcare databases will be defined using the Read clinical code classification system used in primary care, and International Statistical Classification of Diseases and Related Health Problems 10th Revision (ICD-10) used for clinical diagnoses, the Office of Population Censuses and Surveys Classification of Surgical Operations and Procedures 4th revision (OPCS) for procedures and Healthcare Resource Groups (HRG) codes used in HES.

Recording of some variables in healthcare data, such as breastfeeding, is incomplete; we will therefore also investigate the trends in these variables by the mode of delivery using additional data sources such as the National Maternity Surveys.^28^

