### Methods

We will compare rates of diagnosis of asthma and other outcomes of interest over time in children born by CS, comparing outcomes according to whether each mother received preincisional antibiotics.

In the primary analysis, we will estimate a probability that each mother received preincisional antibiotics according to year of birth, based on national policy uptake rates in the year of delivery for primary care data. For secondary care data, we will use the response from each hospital indicating the year of local policy implementation.

The major threat to validity in this observational comparison is not from case-mix confounders (indications for and incidence of CS have changed little over the study period); rather they relate to temporal changes in diagnosis and in the recording of outcomes and other exposures which impact on the number of cases identified in routine data. Patterns of diagnosis of childhood asthma, for example, have changed over time, in part driven by the revisions in the national asthma management guideline and the potentially conflicting compliance and prevalence issues faced in meeting specific indicators of the Quality and Outcomes Framework (QOF) introduced in 2004.^29 30^

An analysis reliant on adjustment for confounding factors is unlikely to succeed in controlling for these changes as it is unclear (1) what all the drivers of all these changes have been, (2) whether any covariates exist which accurately describe these changes without substantial missing data and (3) challenges in specification of a functional form for the relationship between these covariates and outcome.

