#### Sensitivity analyses

Sensitivity to population changes:

Analysis assessing the impact of the timing of the prophylactic antibiotic policy change, including comparison of analysis restricted to the years 2006–2010 (before the change in the NICE guideline) compared with years where over 50% of hospitals had introduced the policy.Analysis of the primary outcomes in the full HES dataset (including data for the hospitals that do not respond to the survey and therefore preclude us linking information about prophylactic antibiotic policy at hospital level) using the estimated probability of introduction of preincisional antibiotics according to calendar year, to investigate the consistency of findings.Analysis investigating the impact of the data recording quality (restricted to HES-linked records in THIN-CPRD database as the most accurate source of records for the mode of delivery).Exploratory sensitivity analysis employing the discordant sibling approach (restricting the analysis to women who gave birth by CS more than once during the study period including before and after the change in the prophylactic antibiotic policy compared with women who gave birth by VD more than once during the study period) to control further for family-related genetic and environmental factors.

Sensitivity to model changes:

Analysis exploring whether the results are robust to the inclusion of a random effect for hospital.

Subgroup analyses:

Exploratory subgroup analysis in HES mother-child linked database by prophylactic antibiotic type administered according to the individual hospital policies to investigate the potential impact of different antibiotics (cefuroxime alone, co-amoxiclav alone, cefuroxime+metronidazole) on child outcomes.Exploratory subgroup analysis by the type of CS (it is hypothesised that children delivered by elective CS have a higher likelihood of asthma and related outcomes and are more likely to be exposed to in-utero antibiotics for longer than children born to women having an emergency CS).

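### The exposure term comes from hospital policy dates, so its coefficient is a policy effect and is not adjusted for misclassification of actual receipt

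*Protocol article*

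**What the plan says.** All places are in the protocol article.

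- **Question.** Under Objectives, the primary objective is "to investigate whether preincisional in-utero exposure to antibiotics immediately prior to birth (Intervention) compared with no preincisional antibiotic exposure (Comparator) increases the risk" of asthma and eczema. Target population likewise contrasts exposed with unexposed children born by caesarean section (CS). The Aim section instead asks about the effect of the change in guidance.
- **What is known.** Timing is not recorded for the individual woman. The strengths and limitations box says that "analysis is based on the estimated proportion of hospitals with the preincision antibiotic policy in each year during the study period". Data sources says: "We will obtain the time point after which preincision antibiotic policy was introduced in each hospital from a national survey".
- **Exposure term.** Under Methods, for primary care: "we will estimate a probability that each mother received preincisional antibiotics according to year of birth, based on national policy uptake rates". For secondary care (HES): "we will use the response from each hospital indicating the year of local policy implementation".
- **Interpretation.** The Analysis section says the Poisson model estimates the relative risk of each outcome with antibiotics before incision rather than after clamping, through a term meant to pick out those who received them early. It then says: "The estimated coefficient will provide an estimate of the change in policy, adjusting for misclassification".
- **Simulation.** Estimates of sample size and statistical power describes a fitted yearly probability of 0 (2006–2009), 0.2, 0.4, 0.6, 0.8 and then 1 (2014–2018). It reports underestimation through misclassification of at most 15% in primary care, with a similar figure for HES.

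**The concern.** One coefficient carries three descriptions: the relative risk of early versus late antibiotics, the effect of a policy change, and an estimate already corrected for misclassification. The first two coincide only if every CS birth under the policy received the dose before incision and none did before the policy. The survey dates policies. Nothing in the article describes data on receipt given the policy.

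The study asks a safety question. The Aim section says that the result will either reinforce the current recommendation or allow harm to be weighed against maternal benefit. Non-receipt and receipt before the policy pull the estimate towards no effect. If readers take the coefficient as a corrected exposure effect, they will understate the risk per exposed child and will not know that an allowance is needed.

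**Working it through.** **Step 1. What the probability term can and cannot correct**

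| Source of error | Covered by the term? |
|---|---|
| Hospital of birth, and so its policy status, unknown (primary care) | Yes, through the yearly share of hospitals with the policy |
| Policy in force, dose not given before incision | No |
| Exposure before incision although the policy was not yet in force | No |
| Policy uptake in the term earlier or later than actual uptake | No |

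**Step 2. Reproducing the article's 15%**

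Inputs from Table 2: CS births exposed 95 107 of 206 615 (THIN-CPRD) and 954 830 of 2 070 500 (HES).

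- Exposed share: 95 107/206 615 = 0.460; 954 830/2 070 500 = 0.461.
- Mean of the fitted term over 13 birth years, assuming equal births per year: (0.2 + 0.4 + 0.6 + 0.8 + 5 × 1)/13 = 7/13 = 0.538.
- Ratio: 0.4603/0.5385 = 0.855 (THIN-CPRD); 0.4612/0.5385 = 0.856 (HES).
- Implied underestimation of the excess risk: 1 − 0.855 = 14.5%, in line with the stated maximum of 15%.

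As a check, Poisson models were fitted to expected counts by birth year, age and mode of delivery (equal births per year and the age pattern are assumptions). With true exposure at about 0.857 of the fitted term, a true relative risk (RR) of 1.16 is estimated as 1.136 to 1.137, an underestimation of 14.1% to 14.8% depending on the model. When true exposure equals the fitted term, the bias is within 1%. So the term removes misclassification only if policy uptake equals receipt.

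**Step 3. What lies behind the 15%**

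- The fitted sequence delayed by one year has mean (0.2 + 0.4 + 0.6 + 0.8 + 4 × 1)/13 = 6/13 = 0.462, close to Table 2's 0.460 and 0.461.
- Exposed share of CS person-years in Table 2: 290 864/792 265 = 0.367; 3 136 942/8 661 832 = 0.362.
- With follow-up of 5 years for births in 2006–2014 and 4, 3, 2 and 1 years for 2015–2018 (55 in total), the delayed sequence gives (5 × 2.0 + 4 + 3 + 2 + 1)/55 = 20/55 = 0.364. Proportional scaling gives (6/7) × 25/55 = 0.390.
- The delayed sequence fits better. In the refits it gives 9% to 17% underestimation, depending on the model.

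The simulated 15% is therefore more consistent with mistimed uptake than with non-receipt. Either way, the fitted term does not remove it.

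**Step 4. Size if receipt is incomplete**

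Let c1 be receipt under the policy and c0 receipt before it, with policy status known.

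Reported RR = (1 + (RR − 1) × c1)/(1 + (RR − 1) × c0)

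The article gives neither c1 nor c0, so these values are assumed.

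| c1 | c0 | True 1.16 reported as | True 1.10 reported as |
|---|---|---|---|
| 1.0 | 0 | 1.160 | 1.100 |
| 0.9 | 0 | 1.144 | 1.090 |
| 0.8 | 0 | 1.128 | 1.080 |
| 0.7 | 0 | 1.112 | 1.070 |
| 0.9 | 0.1 | 1.144/1.016 = 1.126 | 1.09/1.01 = 1.079 |

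With c0 = 0 the excess risk is understated by 1 − c1, that is 10%, 20% or 30%. In the last row it is understated by about 21%.

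**The case against.** The other side has a good deal to say. The sentence at issue itself calls the coefficient an estimate of the policy change. The Aim section asks about the guidance, Methods attributes differences to the change in practice, and the limitations box discloses the proxy. The simulation was set up partly to measure attenuation and reports it. The adjustment claim is true for unknown hospital status. Non-receipt would dilute the maternal benefit estimated in the same data too. All of this stands, and it makes the fault one of definition and claim rather than of concealment. It does not remove the fault, because the objective and the description of the model still speak of exposure, and a disclosed proxy is not an adjusted one.

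A reader might also infer more than the documents support:

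- **That receipt is expected to differ between elective and emergency CS.** The subgroup text says babies born by elective CS are "more likely to be exposed to in-utero antibiotics for longer than children born to women having an emergency CS". That is about duration, not about whether the dose was given.
- **That an upper confidence limit will be used to exclude harm.** No margin or rule of that kind is stated.
- **That HES exposure is coded strictly 0 or 1.** Methods says only that the hospital's reported year is used, and the Analysis section says exposure will not be dichotomous.
- **That the 15% shows non-receipt.** Step 3 shows that a delay in uptake explains it at least as well.

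**Conclusion.** The point holds as one of interpretation. The coefficient is a policy effect. It is adjusted for unknown hospital policy status but not for non-receipt, prior receipt or mistimed uptake, and the unqualified claim in the Analysis section conflicts with the attenuation of up to 15% reported in the sample-size section.

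The size of the dilution is not known. For assumed receipt differences of 0.9 to 0.7 with no receipt before the policy, a true RR of 1.16 would appear as about 1.144 to 1.112. The calculation assumes that the effect applies only to those who received the dose and that receipt is unrelated to baseline risk.

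It would go too far to conclude that the study is bound to report a diluted policy effect as an exposure effect, since several sections already use policy wording. Nor is this a finding about power: the year-by-age event rates are not given, so the stated power could be neither confirmed nor refuted, and it probably includes the simulated attenuation already.

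**What to change.** 1. Define the key parameter, in both the primary care and the HES analyses, as the effect of the hospital's change of policy on children born by CS, and align the wording of Objectives, Target population and Analysis with that.
2. Replace the general adjustment claim with wording such as: *allows for unknown hospital policy status; does not correct for receipt that differs from policy.* State the residual attenuation from the simulation beside it and say what produced it, so that the two sections agree.
3. Add a sensitivity analysis that multiplies the exposure term by an assumed receipt difference c, for example 0.7 to 1.0. In the log-linear model this divides the coefficient and its confidence limits by c, so the implied exposure RR is the estimated RR raised to the power 1/c. For example, 1.128 with c = 0.8 gives 1.128^1.25 = 1.162, close to the 1.16 from which it arose. Report the implied RR with its confidence interval for each c, labelled as resting on assumption.

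No new data are needed: the cost is a few sentences and one table. The real price is that the headline claim narrows from exposure to policy.
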